## Abstract

**Background:**

Mental health is decreasing among young people in Denmark. Our primary aim is to evaluate the effectiveness of a teacher training programme to teach mindfulness as part of regular classroom teaching in Danish upper secondary schools and schools of health and social care on students’ self-reported mental well-being 6 months from baseline. Secondary aims are (1) to evaluate the effectiveness in a vulnerable subgroup as well as in the total population of students 3 and 6 months from baseline using other outcome measures on mental health and (2) to investigate the facilitators and barriers among teachers to implement mindfulness in schools.

**Methods:**

This pragmatic cluster-randomised two-arm superiority trial includes 30 upper secondary schools, 13 schools of health and social care, 76 teachers, and approximately 1100 students aged 16 to 24 years. Our intervention is multi-level and consists of (a) a teacher training programme and (b) a mindfulness programme delivered to students. Students in control schools receive education as usual. Our primary study population is the total population of students. The primary outcome is changes in the short version of the Warwick-Edinburgh Mental Well-Being Scale (SWEMWBS). We also evaluate the effectiveness in a vulnerable subgroup (the 15% with the lowest SWEMWBS score), as well as in the total population of students 3 and 6 months from baseline using other outcome measures on mental health. Data will be analysed using repeated measurement models taking clusters into account. Facilitators and barriers among teachers to implement mindfulness in schools will be investigated through qualitative focus group interviews.

**Discussion:**

The trial will estimate the effectiveness of a population-based strategy on mental health in Danish young people enrolled in education.

**Trial registration:**

ClinicalTrials.gov NCT04610333. Registered on October 10 2020.

## Background

Mental health of children and young people is a global public health challenge [1]. The need to focus on the mental health of young people is gaining increasing recognition as the global community looks to achieve the ambitious Sustainable Developmental Goals (SDG), such as SDG 3: “Ensure healthy lives and promote well-being for all at all ages” [2]. Mental health conditions account for a considerable proportion of the global disease burden during youth and are the leading course of disability in young people [3]. In fact, 75% of mental disorders begin before the age of 24 and 50% by the age of 15 [4]. Suicide is one of the three leading causes of death among older adolescents [5]. Therefore, mental health conditions have huge costs for the individuals affected as well as for society as a whole. The total costs related to mental health problems in Europe are estimated to account for more than EUR 600 billion. Among the European countries, Denmark has the highest costs in terms of % of GDP (5.4%) [6].

However, mental health is more than the absence of mental disorders [7]. Mental health is a fundamental component of the World Health Organization’s (WHO) definition of health. It is conceptualised as a state of well-being in which the individual realises her or his own abilities, is able to cope with the normal stresses of life, can work productively and fruitfully, and is able to make a contribution to her or his community [8]. In this positive sense, mental health is the foundation for well-being and effective functioning for an individual and a community [7].

In Denmark, mental health among young people has been decreasing in recent years. Since 2010, the National Health Profile has reported an increase in the proportion of 16–24-year-olds with poor mental health [9]. A high occurrence of stress, anxiety, tension, and loneliness is seen in this age group as well [10].

According to WHO, mental health is a public issue that requires political priority and action. This is to ensure that effective promotion and prevention are established and that stigmatisation and discrimination are broken down [11]. Mental health promotion and disease prevention in young people can benefit young lives in the short and long term. This stage is deemed as one of the optimal timeframes for intervention, given the neuroplasticity evident in adolescence and the opportunity to step in at a time when the majority of mental health conditions and risky behaviours have their onset [5]. WHO recommends population-based psychosocial interventions to promote positive mental health and prevent mental disorders [3]. Likewise, The Lancet Commission on global mental health and sustainable development emphasise the importance of improving mental health for whole populations [12]. Population-based interventions have the highest and most valuable impact at a society level [13]. The reason for this is that most cases of poor mental health occur among the many who are at low or moderate risk, rather than among the few who are at high risk. In addition, population-based interventions have the potential to improve mental health in all young people as well as in high-risk and vulnerable groups without causing stigma [13].

School environment has been identified as an appropriate setting for providing mental health promotion and prevention. Not least because of its broad reach and central role in the lives of young people [14, 15]. O’Conner highlights the importance of providing school teachers with the necessary skills and knowledge to ensure that the school setting is a beneficial environment for promoting mental health [14]. However, there is a lack of evidence-based intervention content. Moreover, many strategies to improve mental health are designed to be used when people are unwell, and therefore lack relevance for those at low risk and for those who are at high risk, but not currently showing symptoms [16].

Since life cannot be lived without challenges and discomfort, training the ability to handle and be with these challenges in an appropriate way is necessary and beneficial for everyone. One way to train this is through the practice of mindfulness. Mindfulness is a method of mental health training that can be used by anyone, regardless of how they feel. Mindfulness has been defined as the awareness that arises from paying attention on purpose in the present moment, non-judgementally, in the service of self-understanding, wisdom, and compassion [17]. Mindfulness-based Stress Reduction (MBSR) is a well-described group-based programme in mindfulness training developed in 1979 by Jon Kabat-Zinn [18]. The programme consists of eight weekly sessions of 2 ½ hours and one all-day session. The sessions have standardised core elements consisting of different mental and psychical mindfulness exercises. Additionally, there are teachings on stress, stress management, and how to apply mindfulness to interpersonal communication and everyday situations [18]. Today, MBSR is an incorporated part of both mental health promotion, prevention, and treatment worldwide. A Campbell Systematic Review based on 101 randomised controlled trials concludes that MBSR has a moderately large positive effect on outcome measures of mental health when compared to inactive controls. The intervention also improves the quality of life, including social function, and personal development like empathy, coping, sense of coherence, and mindfulness. Compared to active controls, MBSR has an additional small positive effect on outcome measures of mental health, depression, stress, and mindfulness [19].

Given the beneficial effects established by MBSR in adults, there has been an increasing interest in implementing similar initiatives for young people. Research in this area is still preliminary, but growing. Dunning et al. conclude the positive effects of mindfulness-based interventions on mental health in children and adolescents [20]. Their meta-analysis is based on 33 randomised controlled trials. However, there is a high degree of variability in intervention contents and target groups, and the meta-analysis emphasises the importance of incorporating scaled-up trials to further evaluate the robustness of mindfulness-based interventions in youth [20].

The Danish Parliament has funded the Danish Center for Mindfulness at Aarhus University to educate upper secondary school teachers and teachers at schools of health and social care to teach mindfulness to students. The Danish Center for Mindfulness has systematically developed a version of MBSR modified for young people called “On Top of Everything”. It is built on the same overall themes and mindfulness exercises as MBSR, but the duration, number of sessions, and focus in the exercises are adapted to young people in a classroom setting.

## Aims

Our primary aim is to evaluate the effectiveness of a teacher training programme to teach the mindfulness programme “On Top of Everything” as part of regular classroom teaching in Danish upper secondary schools and schools of health and social care on students’ self-reported mental well-being 6 months from baseline. Secondary aims are (1) to evaluate the effectiveness in a vulnerable subgroup as well as in the total population of students 3 and 6 months from baseline using other outcome measures on mental health and (2) to investigate the facilitators and barriers among teachers to implement mindfulness in schools.

## Hypothesis

We hypnotise that young people in the intervention group will improve their mental health during the intervention. We expect to find small effect sizes in the total population of students and higher effect sizes in a vulnerable subgroup [13].

## Methods/design

### Design

The study is designed as a pragmatic cluster-randomised two-arm superiority trial including 30 upper secondary schools and 13 schools of health and social care across Denmark.

### Setting

In Denmark, compulsory education is 10 years (0th to 9th grade). Hereafter, it is up to young people themselves to choose their further education. Two options are included in this research project: upper secondary schools and schools of health and social care. Upper secondary school is an academic youth education programme. It exists in four different forms (HTX, HHX, STX, and HF) which takes 2 to 3 years to complete. The common objective of upper secondary schools is to prepare young people for higher education (e.g. the university) [21]. School of health and social care is a vocational education. It educates social and health care assistants, social and health care workers, and pedagogical assistants over a period of 2 to 4 years. The common objective of schools of health and social care is to educate students on how to take care of people who cannot fend for themselves [22].

### Eligibility criteria

We included Danish upper secondary schools and schools of health and social care with no exclusion criteria. To be able to participate, consent from headmasters/headmistresses was essential. Each participating school was allowed to include between 1 and 4 teachers for teacher training. One of the inclusion criteria for students was an age of 16 to 24 years. Students were able to opt out of the trial by not completing questionnaires.

### Intervention

The intervention is a multi-level, multi-component complex intervention. It consists of a teacher training programme and the mindfulness programme “On Top of Everything” delivered to students. Schools were randomised to begin teacher training in 2020 (intervention group) or in 2021 (control group). The timeline for research activities and intervention content is outlined in Fig. 1 [23]. The teacher training proceeds during a period of approximately 1 year and is facilitated by two MBSR instructors from the Danish Center for Mindfulness, Aarhus University (one with a professional background as an upper secondary school teacher and one as a psychologist).

**Fig. 1 Fig1:**
[figure not shown]
Timeline and description of the research activities and intervention contents in the project

The teacher training programme is based on three parts: First, participation in the MBSR programme, which is delivered in a combination of group-based face-to-face and live online teaching. The aim is to establish a formal mindfulness practice in the teachers. Second, completion of a 4-day residential course including training to teach the “On top of Everything” programme and access to teaching materials. Third, completion of three 2-day supervision seminars on implementation issues and relational competencies based on the work of The Danish Association for Promoting Life Wisdom in Children [24]. The teacher training programme includes information on potential adverse effects associated with mindfulness [25, 26].

The “On Top of Everything” programme consists of 10 well-described, weekly 45–60-min classroom sessions. Each session has a theme and teachers’ notes and body scan, meditation, and yoga recordings.

### Public and participant involvement

Teachers and students have been involved in the development of the “On Top of Everything” intervention through pilot tests.

### Outcome measures

Outcome measures are described in Table 1. Standard participant demographic information (gender, grade, and family setting) was collected at baseline. The outcome measures were collected at three time points (baseline, 3- and 6-month follow-ups). Information about mindfulness practice was collected at 3- and 6-month follow-ups in the intervention group. Our primary outcome is changes 6 months from baseline in the short version of the Warwick-Edinburgh Mental Well-Being Scale (SWEMWBS) [27] in the total population of students. A range of individual-level secondary outcome measures was chosen based on their ability to explore mental health.

**Table 1 Tab1:** Description of the outcome measures assessed at baseline and 3 and 6 months among students

Measurement	Description
Demographic data	Data on age, gender, school, class, and family setting (only baseline)
Warwick-Edinburgh Mental Well-Being Scale. The short version (SWEMWBS) [27, 28]	The SWEMWBS is a seven-item questionnaire measuring mental well-being [27]. All items are positively worded. Participants are asked to rate each item on a 5-point Likert scale ranging from 1 (none of the time) to 5 (all the time) when considering the last two weeks. The overall score is calculated by summing the scores for each item. A higher score indicates a higher level of mental well-being. The scale is a valid and appropriate instrument to measure mental well-being in the Danish population [27]
Strengths and Difficulties Questionnaire. The youth self-report version (SDQ) [29]	The self-report version of the SDQ is a behavioural screening questionnaire measuring subjective well-being and social, emotional, and behavioural functioning among children and youth [29]. It consists of 25 statements, some positively and others negatively worded. Participants are asked to rate each item on a 3-point Likert scale ranging from 2 (very true) to 0 (not true). The 25 items are divided into five subscales of five items each, generating scores for emotional symptoms, conduct problems, hyperactivity/inattention, peer relationship problems, and prosocial behaviour. All subscales except the last one are summed to generate a total difficulties score. The subscales range from 0 to 10 with higher values indicating poorer well-being and functioning for four of the subscales (emotional symptoms, conduct problems, hyperactivity/inattention, and peer relationship problems) and better well-being and functioning for the subscale prosocial behaviour. The total difficulties score ranges from 0 to 40 with higher values indicating poorer well-being and functioning. Goodman et al. have shown that the odds ratio for having a mental disorder was 1.23 (95% CI 1.21 to 1.25) per one-point increase in the total difficulties score and that the odds ratio for developing a mental disorder within a 3-year period was 1.16 (95% CI 1.13 to 1.18) per one-point increase in the total difficulties score [30]. In 2019, Danish SDQ norms were published [31]
Depression Anxiety Stress Scale. The short form version (DASS) [32]	The DASS short-form version is a 21-item questionnaire consisting of three subscales measuring self-rated symptoms of depression, anxiety, and stress [32]. Each subscale consists of seven items. Participants are asked to rate each item on a 4-point Likert scale ranging from 0 (did not apply to me at all) to 3 (applied to me very much or most of the time) when considering the last week. For each subscale, the points are added together and multiplied by two. Thus, it is possible to score between 0 and 42 points on each subscale [33]
Perceived Stress Scale (PSS) [34, 35]	The PSS is a 10-item self-report measure of subjective stress [34]. It consists of 10 questions indicating how often participants have found their life unpredictable, uncontrollable, and overloaded in the past month. All items are scored on a 5-point Likert scale ranging from 0 (never) to 4 (very often) calculating a total sum score between 0 and 40 with higher scores indicating higher levels of stress. The instrument has demonstrated good validity and reliability [35]
Brief Resilience Scale (BRS) [36, 37]	The BRS is a measure of resilience [36]. It consists of six statements, three positively and three negatively worded. Each item is scored on a 5-point Likert scale ranging from 1 (strongly disagree) to 5 (strongly agree). The points are added together and divided by five, calculating a total score with higher values indicating a greater ability to bounce back when experiencing adversity. The following cut-off points have been suggested. Scores from 1.00 to 2.99: low resilience. Scores from 3.00 to 4.30: normal resilience. Scores from 4.31 to 5.00: high resilience. Windle et al. have proposed BRS to be one of the most valid instruments to measure resilience [37]
Experiences Questionnaire (EQ). The decentering subscale [38]	The EQ decentering subscale is a validated 11-item self-report measure of decentering [38]. Decentering refers to the ability to observe thoughts and feelings as temporary and automatic events in the mind, rather than facts or true descriptions of reality. The items of the decentering factor assess three facets: the ability to distinguish one’s self from one’s thoughts, the ability not to automatically react to one’s negative experiences, and the capacity for self-compassion. All items are scored on a 5-point Likert scale ranging from 1 (never) to 5 (always). The total sum score ranges from 11 to 55, with higher scores indicating greater decentering [38]
EQ-5D-Y [39]	EQ-5D is a valid instrument to measure health-related quality of life (HRQoL) for use in economic evaluations. It comprises five dimensions: mobility, self-care, usual activities, pain or discomfort, and anxiety or depression. Furthermore, participants are asked to rate their overall health on the EQ VAS, a vertical scale from 0 (the worst health you can imagine) to 100 (the best health you can imagine)
Three-Item Loneliness Scale (T-ILS) [40]	The T-ILS is a short questionnaire measuring self-reported loneliness [40]. T-ILS consists of three items and is a shortened version of the UCLA Loneliness Scale consisting of 20 items [41]. Participants are asked to answer each question on a 3-point Likert scale ranging from 1 (hardly ever) to 3 (often). The points are added together calculating a total score ranging from three to nine with higher scores indicating a greater extent of loneliness [40]
Karolinska Sleep Questionnaire. Modified version [42]	Sleep problems during the past 4 weeks will be assessed with six items from a modified version of the Karolinska Sleep Questionnaire [42]. The items are responded to on a 5-point Likert scale ranging from 1 (all the time) to 5 (at no time)
Mindfulness practice (those allocated to intervention)	We will use questions on adherence which have been used in former research on mindfulness among children and adolescents [43]

### Sample size

We assume a 1-point increase between-group effect in SWEMWBS to be of public health relevance [44, 45]. From another study that analysed the intervention effect on SWEMWBS in a mixed model with three repeated measurements, and where cluster levels of teacher and school were taken into account, we found a within-person SD = 2.4. To detect an effect on 1 score point in SWEMWBS change, SD = 3.5 = SQRT (2) × 2.4 with 80% power, will require 194 participants in each group, 388 participants in total.

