### Randomisation

#### Sequence generation

The schools were allocated into intervention or control schools in two runs: one for each type of school. Each school received a random number, and then the schools were sorted according to the number of teachers included in the project (1 or 2–4) and the random number. The schools on the list were then alternately allocated to intervention or control starting with a control. This procedure was used to try to balance the two arms according to the teachers included in the project. The allocation was performed using Microsoft Excel.

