### Trial status

In total, 43 schools and 76 teachers consented to participate in the trial (44 teachers from 30 upper secondary schools and 32 teachers from 13 schools of health and social care). Teachers have recruited approximately 1100 students. Three focus group interviews were conducted among teachers in the intervention group after the implementation of the “On Top of Everything” programme.

Teaching of the “On Top of Everything” programme among students in the intervention group took place during the spring semester of 2021. Interviews among teachers took place in June 2021. The last quantitative data (6-month follow-up) were collected among students in the autumn of 2021. We will start cleaning and analysing the data at the beginning of 2023.

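### The 388 students for 80% power come from an individually randomised calculation, although schools are randomised, so the figure assumes no clustering of change

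*Protocol article*

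**What the plan says.** The Design section describes a "pragmatic cluster-randomised two-arm superiority trial including 30 upper secondary schools and 13 schools of health and social care across Denmark". Sequence generation confirms the unit of allocation: "The schools were allocated into intervention or control schools in two runs: one for each type of school".

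The Sample size section sets the target difference: "We assume a 1-point increase between-group effect in SWEMWBS to be of public health relevance". The variability comes from an earlier study analysed with a mixed model, "where cluster levels of teacher and school were taken into account, we found a within-person SD = 2.4". From these it derives "SD = 3.5 = SQRT (2) × 2.4 with 80% power, will require 194 participants in each group, 388 participants in total". The section gives no ICC, cluster size, number of schools, design effect or allowance for loss. Its only mention of clusters concerns the earlier study.

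Under Trial status the article reports that "Teachers have recruited approximately 1100 students", from 43 schools and 76 teachers.

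**The concern.** When schools are allocated, the variance of the difference between arms includes how much schools and classes differ in their average change. A calculation that treats students as independent leaves this out.

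The within-person SD of 2.4 does not put it back. Fitting teacher and school levels in the earlier study removes stable differences between clusters from the residual. Those differences cancel in a change score anyway. What remains unaccounted for is change that is specific to a school or class. This is a natural possibility here, because each teacher delivers the programme to a whole class.

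Two things are at stake. The stated power for the primary outcome does not follow from the stated number. In addition, a reader who sets 1100 recruited against 388 required (1100/388 = 2.8) would infer almost a threefold margin, and that affects how a null primary result is read.

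**Working it through.** **Reproducing the article's figure.** Inputs from the Sample size section: difference 1, SD 3.5, power 80%, equal groups. The significance level is not stated; two-sided 5% is assumed because it reproduces the figure (one-sided 5% gives 152 to 153).

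- n per group = 2 × (1.96 + 0.8416)² × 3.5² / 1² = 192.3. The t-based version is 193.3, so 194 per group and 388 in total.
- The match is exact, so the design effect used is 1.

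**The SD line.** SQRT(2) × 2.4 = 3.394. With that SD the same formula gives 180.8 (t-based 181.8), so 182 per group. The printed 194 belongs to 3.5.

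**Adding the design effect.** Inputs:

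- 43 schools (Trial status), so 43 − 2 = 41 degrees of freedom.
- Spread of school sizes. Table 2 gives teachers per school as 24 schools with 1, 8 with 2, 8 with 3 and 3 with 4. That is 76 teachers, mean 76/43 = 1.767 and SD 0.984, so CV = 0.557 and 1 + CV² = 1.310. This is a proxy for the spread in student numbers.
- ICC of 6-month change: not in the documents; 0.01 to 0.08 assumed.
- Loss to follow-up: not in the documents; 30% assumed as an illustration, leaving 770 of 1100.
- SD 3.5, as the article uses.

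Formulas:

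- DE = 1 + ((1 + CV²) × mean school size − 1) × ICC
- SE = 3.5 × √(4 × DE / N)
- Power from the noncentral t with 41 df, noncentrality 1/SE, critical value 2.02

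Mean school size is 388/43 = 9.02, 1100/43 = 25.6 or 770/43 = 17.9. The multiplier of the ICC is then 1.310 × 9.02 − 1 = 10.8, 32.5 or 22.5.

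| ICC of change | 388: DE | 388: power | 1100: DE | 1100: power | 770: DE | 770: power |
|---|---|---|---|---|---|---|
| 0 | 1.00 | 78.5% | 1.00 | over 99% | 1.00 | 97% |
| 0.01 | 1.11 | 74% | 1.33 | 98% | 1.22 | 94% |
| 0.02 | 1.22 | 70% | 1.65 | 95% | 1.45 | 90% |
| 0.05 | 1.54 | 60% | 2.63 | 81.5% | 2.12 | 76% |
| 0.08 | 1.87 | 52% | 3.60 | 68% | 2.80 | 64% |

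The first row shows that about 1.5 points of the shortfall at 388 come from using 41 degrees of freedom, not from clustering.

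The effective size of 1100 students (1100/DE) is about 667 at ICC 0.02, 419 at 0.05 and 305 at 0.08.

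**Sensitivity.**

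- With equal school sizes, power at ICC 0.05 is 64% for 388 students and 87% for 1100.
- With SD 3.394, power at 388 is 77%, 73% and 63% at ICC 0.01, 0.02 and 0.05.
- Spreading 388 students over all 43 schools is favourable to the article. Recruitment requires a class of at least 15 from each teacher, and 388 students in fewer, larger schools would give less power.

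**The case against.** The strongest defence is that the calculation agrees with the planned model. It works on change, and Statistical methods lists random effects of school, teacher/class and student, with no term for clusters changing differently over time. Under that model, stable cluster effects cancel and 388 students give the stated power. The shortfall therefore depends on an ICC that the documents do not supply.

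This stands to a point. No particular power below 80% is proven, and the figures above are conditional. It does not rescue the paragraph, because zero clustering of change is a strong assumption that is nowhere stated or justified.

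A reader might go further and infer that the trial is underpowered. The documents do not support that. About 1100 students were recruited, and power stays above 80% up to an ICC of about 0.05 on these assumptions. It falls below 80% only towards the top of the assumed range, or at 0.05 with the assumed 30% loss. The planned analysis also already includes school and class effects.

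The SD slip is small and errs on the safe side, asking for 388 − 364 = 24 more students. It may be rounding: an unrounded 2.44 prints as 2.4 and gives 3.45, which prints as 3.5.

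**Conclusion.** The claim that 388 students give 80% power is wrong as written for a trial that randomises schools. It is the independent-student number, and it holds only with no school- or class-specific change. For an assumed ICC of change of 0.01 to 0.05, power at 388 is about 74% to 60%, against 78.5% at ICC 0 with 41 degrees of freedom. These values also rest on SD 3.5, two-sided 5% and a school-size CV taken from teacher numbers.

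The finding concerns the printed justification, not the adequacy of the trial as recruited. Equally, 1100 against 388 should not be read as nearly a threefold margin, because the effective size shrinks as the ICC rises. The SD line is a minor inconsistency that does not alter the conclusion.

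**What to change.** Restate the Sample size paragraph for the design that was used. Give the SD of change, the design effect formula shown above, 43 schools, about 25.6 students per school, a CV of about 0.56 with its source, and a stated range of ICCs of change. Label the ICCs as assumptions unless the earlier study can supply an estimate. Replace the statement that 388 students give 80% power with the power at about 1100 students, with and without an assumed loss. State the significance level and sidedness.

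In the same edit, make the SD line agree with itself: either print the unrounded within-person SD, or use 3.39 with 182 per group before the design effect.

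The cost is one reworded paragraph and a stated figure that looks less favourable. Data collection ended in autumn 2021, and no extra recruitment or change in conduct is needed.
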